### ***The number of subjects planned to be enrolled***

***In multicentre trials, the numbers of enrolled subjects projected for each trial site should be specified. Reason for choice of sample size, including reflections on (or calculations of) the power of the trial and clinical justification***

To account for cluster randomisation, sample size calculations are based on recent sample size requirements developed by Heo & Leon (2009) to detect intervention by time interactions in longitudinal cluster randomized clinical trials. This trial will be powered to detect differences in the overall sample as well as in the high-risk students also. To allow for comparisons between the high-risk students, 600 high risk students from 20 schools are required (i.e. 30 high-risk students per school and 5 schools per intervention group). This would achieve 80% power to detect a standardized between-group mean difference of 0.3 ( $p = 0.05$ ) in outcomes at the end of the trial with 7 measurement occasions. An effect size of 0.3 is comparable to previous trials of drug prevention programs (Cuijpers, 2002; Tobler & Stratton, 1997). To account for dropouts during the trial which we expect to be approximately 10% ([name] et al., 2009a; [name] et al., 2010), we aim to recruit 80 students per school, 40% ( $n = 32$ ) of whom are expected to be high-risk based on previous research CI [name], and 6 schools per group giving us a total of 1920 students from 24 schools at baseline to test the effect of the intervention in the overall group.

***The level of significance to be used***

All tests conducted will use a predetermined alpha level of .05.

***Criteria for the termination of the trial***

There are no criteria for the termination of the trial. There have been no significant adverse events in prior research to indicate termination is necessary.

***Procedure for accounting for missing, unused, and spurious data***

The appropriate longitudinal statistical methods will be used that account for missing data.

***Procedures for reporting any deviation(s) from the original statistical plan  
(any deviation(s) from the original statistical plan should be described and justified in  
protocol and/or in the final report, as appropriate)***

Any deviations from the original statistical plan will be described and justified in an amendment to this protocol.

***The selection of subjects to be included in the analyses  
(e.g. all randomized subjects, all dosed subjects, all eligible subjects, evaluable subjects)***

All randomised participants will be included in the overall efficacy analyses.

## Direct Access to Source Data/Documents

***The sponsor should ensure that it is specified in the protocol or other written agreement that the investigator(s)/institution(s) will permit trial-related monitoring, audits, IRB/IEC review, and regulatory inspection(s), providing direct access to source data/documents.***

In relation to data and safety monitoring, the Chief Investigators and the Project Coordinator will meet regularly with the Research Officers and Research Psychologists to assure the proper conduct of the study and the safety of participants. This will involve monitoring the data collection and data entry and reviewing any adverse event reports that may arise.

Progress reports will be submitted annually to the NHMRC by 31st March (for the previous year). This report will provide information relevant to the achievements of aims of the study for each of the 5 years of funding.

Figure 3. NHMRC Progress Report template

### PROGRESS REPORT ON RESEARCH ACTIVITY

The National Health and Medical Research Council (NHMRC) requires all NHMRC Administering Institutions that have signed a Funding Agreement with NHMRC to continue to meet the requirements of the Funding Agreement. The Funding Agreement requires the Administering Institution to ensure that a Progress Report prepared by the Specified Person in relation to an ongoing Research Activity is submitted to NHMRC by the date specified in the Funding Policy.

The purpose of the Progress Report is to collect information relevant to the achievements of aims against those specified in the application for each Research Activity.

This form should be used for reporting on the following types of funding schemes:

- CRE grants
- Development Grants
- Partnership project Grants
- Program Grants
- Project Grants (including European Union Projects)
- Strategic Awards (including Targeted Calls for Research and NHMRC EU Collaborative Research Grants)

Information provided in the Progress Report will be used to assist NHMRC to satisfy legislative requirements in relation to its administration of funding. Reports will be assessed by NHMRC staff. Failure to complete and submit this report may result in funding of a Research Activity being suspended until the Report is provided.

A signed electronic version of the Progress Report should be emailed by your RAO to: [[contact]](mailto:[contact]).

Questions regarding Progress Reports should be referred to the Research Administration Section by telephoning [name] or emailing [[contact]](mailto:[contact])

Figure 3 (continued). NHMRC Progress Report template

**SECTION A – Administration details****Administering Institution****NHMRC Application ID****Chief Investigator A****Title of Research Project****Type of Research Grant****(eg. Project Grant)****Year of Funding to which this report  
applies (eg. 1,2,3 etc)****SECTION B –Progress against the research aims**

1. Have the aims or objectives outlined in the application changed since funding was awarded for the project?

(Please circle a response)

YES NO

2. If the answer to Q1 is YES, please explain why the aims have changed (eg. If aims changed because the amount of funding sought was reduced, please advise below)

## Figure 3 (continued). NHMRC Progress Report template

3. Is satisfactory progress towards achieving the stated research aims being achieved?  
(Please circle a response) YES NO

4. If the answer to Q3 is NO, please explain why satisfactory progress has not been achieved

|  |
|--|
|  |
|--|

5. Has your on-line CV been updated to reflect all current publications associated with this research activity?  
(Please circle a response) YES NO

(Note: In examining reports, NHMRC may wish to use details of publications contained within the CV loaded in RGMS. Therefore it is preferable that this is kept up to date.)

## **Quality Control and Quality Assurance**

The Climate Schools intervention and assessments will be administered online so that quality is controlled and assured.

## **Ethics**

Please see the attached UNSW HREC Ethics Application (HREC 11274) and associated attachments. Also refer to the UNSW HREC reply (dated 22/07/2011) and reply from the Investigators (dated 3/8/2011).

**Data Handling and Record Keeping**

All computer files containing the collected data will be password protected and only those directly involved in the project will have access. Hard copy consent forms, student lists (including student's unique codes to link their surveys over time), and de-identified surveys, will be stored separately in locked filing cabinets. Only the research staff directly involved in the project will have access to them. Data collected as part of the assessment and treatment components of the trial will be recorded in PASW Statistics 18 by the Research Officers employed on the study.

**Financing and Insurance****TYPE OF FUNDING**

NHMRC Project Grant - Standard Project Grant

**PERIOD OF FUNDING**

5 year(s) of funding has been approved for this project

Start date 1 January 2011

End date 31 December 2015

Final date by which the project must commence 30 June 2011

FUNDS, FUNDING - Total Funding amount is: \$723665

**APPROVED BUDGET**

| Year         | 1        | 2        | 3        | 4        | 5       |
|--------------|----------|----------|----------|----------|---------|
| TOTAL | \$178902 | \$224599 | \$143205 | \$143205 | \$33754 |

Funding Payments are scheduled quarterly in advance.

Note: GST and an annual indexation may be applied to some components of this budget.

*\*This information was obtained from NHMRC App 1004744 Schedule.*

This project will be carried out in accordance with UNSW insurance policies.

**Publication Policy**

Findings will be published in peer reviewed journals throughout the trial and at the conclusion. All CIs and research staff on the time will be involved in preparing these for submission. Participating schools will also be sent the results and have the option to share these with parents and students.

## Project Description Template

### 1. Lay Summary & Aims (Maximum of 500 words)

Briefly provide a summary of the project in lay terminology (no more than 500 words).

The project summary should include the following details:

- Aims of the project
- Importance of the study

In 2011, CIs [name], [name], [name] and [name] (NHMRC APP1004744; HREC 11274) initiated the *Climate and Preventure* (CAP) study: the first ever randomised controlled trial (RCT) of a comprehensive school-based drug prevention model combining two complementary approaches: *universal* prevention, which is delivered to all irrespective of level of risk, and *selective* prevention, which is tailored for adolescents with personality vulnerabilities that increase risk for alcohol and other drug use. Twenty-six schools and 2,190 participants (aged 13-14) were recruited to the CAP study in 2012 and students completed five self-report assessments over 3 years. Participant retention is high, ranging from 71 to 83% over the 3-year follow up. Results at 3 years demonstrate the effectiveness of universal *and* selective approaches in preventing harmful alcohol use among low- and high-risk adolescents, the additive benefits of universal and selective prevention for reducing cannabis uptake in high-risk adolescents, and the effectiveness of both universal and selective prevention in reducing aggression among high-risk adolescents. Worldwide, little is known about the effectiveness of drug prevention approaches beyond 3 years. Therefore, the aim of the present study is to extend the follow-up of the CAP Study cohort over the critical transition from adolescence into early adulthood.

Original ethics approval (HREC 11274) expired on the 15th of August 2016 and a 3-month extension was subsequently granted. We are now seeking approval to conduct ongoing research to determine the long-term effectiveness of the CAP intervention. In particular, this research aims to answer the following questions:

1. What is the long-term effectiveness of universal, selective and combined alcohol and drug prevention into early adulthood (ages 18-21)?
2. Are selective and universal alcohol and drug prevention effective in reducing aggressive behaviour and violent offending into early adulthood?
3. What are the mechanisms of change underlying the intervention effects?

This project will be the first in the world to examine whether combining *universal* and *selective* drug prevention strategies enhances durability of effects in the longer-term, over a 7-year period from adolescence to early adulthood.

This is an important transitional period with unique challenges and increased susceptibility to alcohol and cannabis use and related harms. It will answer critical questions about the potential benefits of these approaches in reducing alcohol and drug-related violence during the high-risk early adulthood period. Further, it will provide crucial information about the underlying mechanisms of change and inform future refinements to achieve even more powerful prevention effects.

### 2. Background Literature Review – (Maximum of 500 words)

Provide an outline of the theoretical background for the research proposal with reference to relevant literature.

- The background literature review should be "based on a thorough study of the current literature, as well as previous studies" (NS 1.1c) along with;
- The potential significance of the study

Young adulthood in Australia is characterised by increased use of alcohol and cannabis ([name] et al., 2010; Hall et al., 2016). Within a 12 month period, 1 in 3 young Australian adults consume alcohol at very high risk levels and 1 in 5 use cannabis (AIHW, 2013). At this age, episodes of intoxication can have significant health, legal, social and financial consequences, including risk of impaired neurocognitive function and development (Hall et al., 2016). In addition, patterns of use established during early adulthood increase risk of developing substance use disorders and co-morbid mental health problems, all of which negatively impact on current functioning and future life options (Hall et al., 2016). Among young people aged 20-24, alcohol and other drug use is among the leading contributors to total burden of death, disease and injury, accounting for an estimated 14% of total disease burden (Degenhardt et al., 2016). The substantial harm related to drug and alcohol use is in part attributable to the associated risk of violent behaviour, including assaults, homicides, self-harm and suicide (Hall et al., 2016). For example, toxicology reports from a national coronial inquiry in Australia found that alcohol and/or drug (primarily cannabis) use was involved in 78% of "King hit" (single incapacitating blow to the head) cases between 2000 and 2012 (Pilgrim et al., 2014).

Despite the considerable harms attributable to alcohol and drug use, our prevention evidence base in this age group is

weak. Adolescents with personality risk factors for alcohol and other drug use, such as impulsiveness and sensation-seeking (Castellanos & [name], 2012; [name] et al., 2016), may be particularly susceptible during this period of new found autonomy. The transition to young adulthood also encompasses legal access to alcohol at 18 years in Australia, and increasingly regular drinking or other drug use may emerge as a way of forming new friendships and/or coping with the increasing life stressors and demands that emerge at this stage. Our own investigations highlight the importance of coping motives for alcohol use (i.e. drinking to cope with negative emotions such as anxiety or hopelessness), which are strongly associated with alcohol-related harms during this early period of adulthood (Stapinski et al., 2016). Despite the unique challenges and increased susceptibility during this transitional period, few studies have examined the effectiveness of drug and alcohol prevention approaches beyond secondary school. There is limited evidence from studies in the United States (Spath et al., 2016; Spath et al., 2015; Ellickson et al., 1993) that receiving the universal Botvin Life Skills Training in Year 6-7 (ages 12-13) reduced risk of alcohol-related problems and illicit drug use into early adulthood (ages 18-22). The long-term effectiveness of selective prevention approaches (such as *Preventure*), and the combination of skills development within a social influence model (such as *Climate*) is unknown.

The CAP trial cohort is now approaching early adulthood and represents a unique opportunity to examine the impact of universal and selective prevention on developmental pathways to alcohol and cannabis harms in young adults. These two prevention approaches have different strengths: while universal approaches have the capacity to reduce alcohol and drug use on a wider scale (Botvin et al., 2007), selective approaches are optimal for youth at high risk of drug and alcohol misuse due to an underlying vulnerability ([name] et al., 2008). Along with increased exposure to alcohol and cannabis during early adulthood, high-risk personality styles may become more pronounced with the onset of new challenges, increased autonomy, and formation of new friendship circles (Elkins et al., 2006). The CAP study provides a unique opportunity to examine whether high-risk young people are less responsive to universal interventions (Faggiano et al., 2007), and may gain greater benefits in the longer-term from selective programs which target the underlying risk factors for drug and alcohol use ([name] et al., 2008).

The durability of universal and selective prevention effects into early adulthood is a crucial research question, as the choices young people make during this important life stage can have profound effects for many years to come. The CAP trial is the first in Australia to adapt and evaluate the selective *Preventure* program, and the first ever trial of a comprehensive prevention model combining selective and universal interventions. Our international team is uniquely placed to capitalise on this window of opportunity with our existing trial cohort to address the gap in knowledge about longer-term outcomes of alcohol and drug prevention.

### 3. Research Design and Methodology (Maximum 1 page)

Provide an outline of the research design, the study timeline and data collection methods.

#### **Study Design**

Participating schools in the CAP study (2012-2015) were randomised to one of four conditions: Climate, Preventure, Climate and Preventure (CAP) or control (see *Figure 2*). Following the baseline assessment at the start of Term 1, students in the intervention groups received the (online) *Climate Schools* and/or (2 session, manualised) *Preventure* programs during Terms 1 and 3 of Year 8.

The *Climate Schools* program is based on the effective harm-minimisation approach to prevention and aims to reduce the use of alcohol, cannabis and related harms among young people through computer-delivered cartoon storylines which impart information about the short- and long-term effects of alcohol and cannabis, normative alcohol and cannabis use, refusal skills, and first aid. The program was pioneered by CI [name], CI [name] and AI [name] ([name] et al., 2009a; 2009b; 2009c; McBride et al., 2006; Vogl et al., 2009) and consists of twelve 40-minute lessons and is designed to fit within the school health curriculum.

The *Preventure* program is a brief personality-targeted substance use preventive intervention for high-risk adolescents aged 14-15 years. Young people with high scores on four personality risk-factors for early-onset substance misuse and other risky behaviours (i.e. Sensation Seeking, Impulsivity, Anxiety Sensitivity and Hoplessness (Woicik et al., 2009)) participate in two 90 minute group sessions with a trained facilitator and co-facilitator aimed at addressing maladaptive coping behaviours. Only students who scored 'high-risk' on any one of the four personality subscales on the SURPS received the *Preventure* only program.

Students in the CAP condition received a combined intervention involving the universal Climate Schools intervention as well as the targeted Preventure intervention. Students randomised to the control group received their usual health education

[figure not shown]

classes (including lessons on drugs and alcohol), and were offered the use of the *CAP intervention* following completion of the study.

[figure not shown]

Figure 2. CONSORT diagram showing design and participants recruited into the original CAP trial.

## Schedule of Assessments

Table 1 shows assessments completed as part of the original CAP trial, and proposed extended follow-up assessments. Using multiple sources of locator information already provided to the research team, all participants will be invited to complete online assessments at 5-, 6- and 7- years. Participants will complete surveys online via the CAP study website ([www.capstudy.org.au](http://www.capstudy.org.au)). Participant responses will be linked over time using a unique identification code to ensure confidentiality.

Table 1: Completed CAP study assessments and timeline for extended follow-up assessments

| Original CAP trial                                                                                                                         |                                             |                                             |                                             | Timeline for Extended Follow-up |                   |                |
|--------------------------------------------------------------------------------------------------------------------------------------------|---------------------------------------------|---------------------------------------------|---------------------------------------------|---------------------------------|-------------------|----------------|
| 2012                                                                                                                                       | 2013                                        | 2014                                        | 2015                                        | 2017                            | 2018              | 2019           |
| Year 8                                                                                                                                     | Year 9                                      | Year 10                                     | Year 11                                     | Post-school +1                  | Post-school +2    | Post-school +3 |
| Baseline + Intervention
n = 2,190                                                                                                | 1-year F/U survey
n = 1,818 (83%) | 2-year F/U survey
n = 1,732 (79%) | 3-year F/U survey
n = 1,601 (71%) | 5-year F/U survey               | 6-year F/U survey | 7-year F/U     |
| Court Records of Drug and Violent Offending accessed through retrospective data linkage                                                    |                                             |                                             |                                             | ↔                               | ↔                 | ↔              |
| Note. Results will be disseminated via conference presentations, peer-reviewed journal articles, community webinars and teacher workshops. |                                             |                                             |                                             | Statistical Analyses            |                   |                |
|                                                                                                                                            |                                             |                                             |                                             | Dissemination of results        |                   |                |

## Measures

Demographic data including gender, age, academic performance, and truancy rates have been collected at baseline. To allow for modelling of outcomes over a 7-year period, extended follow-up measures will be consistent with those administered during the original trial. All assessments will involve self-report using well validated instruments. Self-report is the favoured method of assessment for young people for assessment of drug and alcohol use symptoms and has been found to have excellent discriminant and predictive validity (Crowley et al., 2001). To corroborate reports of aggression and alcohol/drug related harms, consent will be sought to match participant data with court record data held in the Reoffending Database at the NSW Bureau of Crime Statistics and Research (BOCSAR).

### a) Primary and Secondary Outcomes (RQ1 and RQ2)

*Binge-drinking and Cannabis use* will be assessed using an adapted version of the Patterns of Alcohol index (McBride et al., 2004), and cannabis questions from the National Drug Strategy Household Survey 2013 (AIHW, 2013). These measures allow for comparison with a large scale representative group of Australians. *Alcohol and Cannabis-related harms* will be measured using an abbreviated version of the Rutgers Alcohol Problem Index (White et al., 1989); and a 6-item scale will be used to assess cannabis related harms (Copeland et al., 2005). The DSM-5 self-report symptom checklist developed by Batterham et al (2016) will be administered to assess emerging symptoms of alcohol and other drug use disorders and other psychiatric symptoms as participants enter adulthood. *Aggression* will be measured using the Reactive-Proactive Aggression Questionnaire (Raine et al., 2006). Self-reported violence will be measured using a 7 item violence scale validated in the Dunedin longitudinal study (Arseneault et al., 2000). To corroborate self-report measures and to further examine the criminal involvement of this group as well as hypothesised intervention effects on drug-related violent offending, consent will be sought to match participant data with court record data from the Bureau of Crime Statistics and Research (BOCSAR). The Reoffending Database contains detailed court records of every individual who has appeared in the Children's, Local, District and Supreme Criminal Courts of NSW since 1994. Drug-related offences over the period from 2012 (baseline) to 2019 and violent offending (homicide, assault) from 2012 to 2019 will be examined through data linkage to the Reoffending Database. To analyse mortality outcomes and to ensure that no deceased persons are contacted to participate in follow-up surveys consent will also be sought to link CAP study participant survey data with the National Death Index at the Australian Institute of Health and Welfare.

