## 7. Consent

Provide a detailed description of the consent process to include the following:

- The type of consent that will be sought (e.g. verbal/ written/ return of survey etc.), how and when you will provide consent materials to your potential participants and why this method of consent is appropriate for the participant population.
- How, when and to whom participants will indicate their consent and how any real or perceived coercion will be avoided during the consent process.

**\*\*if the project involves the use of data already collected and the participants have already provided their consent for this to happen, please attach a copy of the original consent form as evidence.**

**\*\*if you are seeking a waiver of consent, please provide justification. (See the National Statement, Chapters 2.2 and 2.3 for more information).**

In line with follow-up procedures used in waves 1-4, participants will be contacted via email or phone in 2017 and will be invited to consent to completing three additional surveys. Participants will also be asked for consent for their name and date of birth to be released to the Reoffending Database at the Bureau of Crime Statistics and Research (BOCSAR), and to the National Death Index (NDI) Database at the Australian Institute of Health and Welfare (AIHW).

Linking to the Reoffending Database at BOCSAR will allow for an objective measure of drug and alcohol related problems and self-reported aggression and criminal involvement. This is particularly important given the strong association between drug use and crime where two in every three offenders (66%) who are detained by police are under the influence of at least one drug – not including alcohol (Payne & Gaffney, 2012). Participants will be advised that, should consent be given for data linkage, the information collected will be offence type, date of offence and penalty. Participants will be asked to consent to data linkage occurring on three occasions (2017, 2018 & 2019). Participants will be informed that this information will be collected to better understand the relationship between drug use and crime with the aim of informing prevention initiatives.

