Linking of participant data to the NDI at the AIHW will allow for a deeper understanding of the relationship between substance use, mental health, psychological and environmental factors. Participants will be informed of the exact information that will be obtained from the NDI. Participants will be advised that, should consent be given, the information that will be requested will be all information stored in the NDI database, fact of death information (e.g. date of death, state/territory the death was registered in, year the death was registered) and cause of death information (e.g. underlying and other causes of death). Participants will also be asked for consent to repeat data linkage with NDI i.e. for each of the three follow-up survey occasions in 2017, 2018 and 2019. Participants will be informed that this data will be utilised to analyse survival rates and mortality outcomes of CAP study participants, and also to ensure that no deceased persons are contacted to participate in follow-up surveys.

It will be stressed to participants that they are not required to consent to the data linkage, and can withdraw consent from data linkage or other aspects of the study at any time. The participant information sheets state clearly that involvement in the study is voluntary and that a decision whether or not to participate will not prejudice future relations with The University of New South Wales or the researchers (see attachment). It also states that participants are free to

withdraw at any time without giving a reason and without penalty.

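### Record linkage starts only with consent sought in 2017, so deaths before then cannot be seen, death screening cannot cover the 2017 contact, and court records will describe a consenting subset

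*Protocol*

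**What the plan says.** All references are to the Project Description for the extended follow-up, within the Protocol.

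- **Death index, purpose.** Section 3, Measures a), names mortality analysis as one aim of linkage. It adds a second, "to ensure that no deceased persons are contacted to participate in follow-up surveys consent will also be sought to link" the survey data to the National Death Index. Section 7 (Consent) repeats both aims and says that "this data will be utilised to analyse survival rates and mortality outcomes of CAP study participants".
- **When consent is sought.** Section 7: "participants will be contacted via email or phone in 2017 and will be invited to consent to completing three additional surveys". Linkage consent is requested in the same approach: "Participants will also be asked for consent for their name and date of birth to be released to the Reoffending Database", and likewise for the death index.
- **Repeat linkage.** "Participants will be asked to consent to data linkage occurring on three occasions (2017, 2018 & 2019"; section 7 sets the same three years for the death index.
- **Voluntary and revocable.** Section 7 tells participants that "they are not required to consent to the data linkage, and can withdraw consent from data linkage". Section 10 makes release of identifiers to the court-records agency conditional on the participant's consent.
- **Court-record window.** Section 3, Measures a): "Drug-related offences over the period from 2012 (baseline) to 2019 and violent offending (homicide, assault) from 2012 to 2019 will be examined" by linkage to the Reoffending Database. The same paragraph gives these records two roles: to corroborate self-report, and to examine hypothesised intervention effects on drug-related violent offending.

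**The concern.** The consent step fixes who can ever appear in the linked data, and it comes about five years after baseline. For mortality, a person must be alive, located and willing in 2017 to be linked at all. The plan speaks of survival among the study's participants without giving a start date or limiting the statement to consenters. If survival were counted from the 2012 baseline, everyone linked would have survived to consent by construction, in every arm.

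The screening aim is circular for the first contact. The only route to the death index is to contact the person and obtain agreement, so the index cannot show beforehand that the person has died. That is also the contact before which the most years have passed since baseline.

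For offending, participants decide in 2017 about a record that largely exists already. Section 7 says they will be told that offence type, date and penalty are collected. Whether a record is available can therefore depend on what it contains. At stake are the reported level of offending and, under a further condition examined below, the comparison between arms.

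**Working it through.** The plan gives no event count, power or consent rate for the linked outcomes, so it has no figure to reproduce. The check is one of dates and logic, followed by illustrations on assumed rates.

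**1. Unobservable period for deaths.** Inputs: baseline 2012, consent sought in 2017, last linkage 2019 (sections 3 and 7).

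(2017 − 2012) / (2019 − 2012) = 5/7 = 71%.

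No death in those five years can enter the linked data. Deaths after consent, among consenters, can be found at later linkages.

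**2. Number of deaths involved.** Input: 2,190 participants (section 4). The death rate is an assumption, taken over 10 to 100 per 100,000 per year.

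- 2012 to 2017: 2,190 × 5 × rate = 1.1 to 11.0 deaths, none linkable.
- 2017 to 2019: 2,190 × 2 × rate = 0.4 to 4.4 deaths in the whole cohort. Only those among consenters are linkable; at an assumed 50% consent, 0.2 to 2.2.

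**3. Screening for deceased persons, by survey.**

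| Survey | Consent already held? | Can the index screen the contact? |
|---|---|---|
| 2017 | No, it is requested at this contact | No |
| 2018 | Yes, for consenters | Yes |
| 2019 | Yes, for consenters | Yes |

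Section 6 adds that only those who consent are contacted again, so the index can serve only the two later contacts.

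**4. Offending under selective consent.** Let p be the true prevalence, and cO and cN the consent rates among offenders and non-offenders. The linked prevalence is

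p·cO / [p·cO + (1 − p)·cN].

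*Level.* Assume p = 4%, cO = 30%, cN = 60%: 0.012 / (0.012 + 0.576) = 2.0%.

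*Comparison between arms.* The odds of offending in the linked set equal the true odds × cO/cN. If cO/cN is the same in both arms, it cancels from the odds ratio. With cN = 70% in both arms (assumed):

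| True control / intervention | Offender consent, control / intervention | Linked rates | Linked risk difference | Linked odds ratio (true) |
|---|---|---|---|---|
| 5% / 3% | 40% / 40% | 2.9% / 1.7% | −1.2 points (true −2.0) | 0.588 (0.588) |
| 5% / 3% | 40% / 50% | 2.9% / 2.2% | −0.8 points (true −2.0) | 0.735 (0.588) |
| 5% / 3% | 50% / 40% | 3.6% / 1.7% | −1.9 points (true −2.0) | 0.470 (0.588) |
| 5% / 5% | 40% / 40% | 2.9% / 2.9% | 0 | 1.00 (1.00) |
| 5% / 5% | 40% / 50% | 2.9% / 3.6% | +0.7 points (true 0) | 1.25 (1.00) |
| 5% / 5% | 50% / 40% | 3.6% / 2.9% | −0.7 points (true 0) | 0.80 (1.00) |

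Equal selection lowers the rates and shrinks the risk difference, leaves the odds ratio unchanged, and creates no false effect when there is none. A false effect needs selection that differs between arms.

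**The case against.** Several counter-arguments have force.

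*The survival analysis is not void.* A reader might infer that it is guaranteed to show no deaths throughout. The documents do not support that: linkage is repeated in 2018 and 2019, so deaths among consenters after consent are captured. Nor does the plan state that survival time starts in 2012; only the court records carry that start date. A delayed-entry analysis fits the text and may be in an analysis plan that is not shown. What remains is that no analysis plan can recover deaths before consent, and the wording on survival of study participants does not acknowledge this.

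*Mortality is peripheral.* None of the three research questions in section 1 concerns it, and step 2 suggests few events on any of the assumed rates. This limits the weight of the mortality point, but it does not touch the screening claim, which is wrong for 2017 however many deaths there were.

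*Research question 2 does not rest on court records.* A reader might infer that it is answered in a sample selected on its own outcome. Section 3 lists a self-report aggression questionnaire and a self-report violence scale, and brings in court records partly to corroborate them. This objection stands in large part. The same section also wants court data for intervention effects, and section 7 calls them objective, so their standing needs to be stated.

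*Bias between arms is not shown.* This stands. No consent rate appears in the documents, by arm or by offending. Differential consent is plausible, since section 1 reports effects of the programmes on aggression, but it is an assumption.

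*Individual consent is an ethical constraint.* It is, and the point does not ask for it to be removed. Linking all 2,190 without consent might look like the remedy, but section 7 mentions a waiver only in the form's printed instructions. It would also take in people who have withdrawn and conflict with the consent condition in section 10.

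**Conclusion.** The point holds in a limited form. From the plan's own dates and consent rules, with no assumed figures:

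- deaths from baseline to consent, about 5 of 7 years, cannot be observed through linkage, so survival of the cohort from baseline cannot be estimated from linked data;
- death-index screening can protect the 2018 and 2019 contacts but not the 2017 contact;
- court records for 2012 to 2019 will describe a self-selected subset.

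The consequences for offending depend on assumptions. If offenders consent less often, prevalence is understated, by about half in the 4% example. If that selection also differs by arm, the odds ratio shifts: offender consent of 40% against 50% moves a true 1.00 to 1.25 or 0.80. This is a risk to guard against, and the documents do not establish that the comparison is biased. All death rates, offending rates and consent rates used here are illustrative.

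**What to change.** 1. In section 3, Measures a), and section 7, define linked mortality follow-up as starting at each person's consent date (delayed entry), among consenters only. State that no linked survival will be reported from 2012 to consent in 2017.
2. In the same two places, say that screening for deceased persons applies only after the first contact and consent, that is, to the 2018 and 2019 surveys.
3. State that the self-reported aggression and violence measures carry research question 2, with court records as supportive evidence from a consenting subset.
4. Report linkage consent by arm. Add a sensitivity analysis that weights linked cases by their probability of consent, estimated from data already collected from baseline to year 3, such as aggression and substance use, with truancy from baseline. Weighting removes only the selection that those data explain.

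The cost is a few sentences of wording, slightly more analysis work and a narrower mortality claim. No new data collection is needed, and the consent arrangements stay as they are.
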